### Design and Randomization

The stepped-wedge cluster design accounts for the proportion of the study period that each group spends in the control and intervention periods (Table 1).

Randomization will occur at the unit level. There are 2 units at HUP-Cedar; using a random number generator, the first unit will be chosen. Eight weeks later, the second unit will begin Thrive referrals. Each unit has 1 case manager and 1 social worker responsible for discharge planning and initiating Thrive referrals. Due to the small number of clinicians and their shared workspace, all 4 will be trained simultaneously, and concealing allocation will not be feasible.

**Table 1 table1:** Study diagram for the type I hybrid effectiveness-implementation, stepped-wedge, cluster randomized controlled trial of the adapted Thrive clinical pathway for serious mental illness.

Cluster	Baseline (3 months)	Enrollment period 1 (two months)	Enrollment period 2 (two months)	Follow-up (17 months)
Sequence 1 (first unit)		✓	✓	✓
Sequence 2 (second unit)			✓	✓

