### Variables and Measures

The primary independent variable is participation in Thrive. The outcome variables include Thrive referral rates; 30-, 60-, and 90-day readmissions and ED visits; and receipt of primary and specialty care within 30 days of index hospitalization [23-25]. For Thrive participants, these outcomes will be assessed from the date of hospitalization that resulted in a referral to Thrive. For the usual care group, we will identify all readmission and ED visits occurring after the first index hospitalization identified in the EHR from the calendar year of the study. Additional covariate data at both the patient (eg, demographics, comorbidities, or mental health diagnoses) and unit levels (eg, type of unit, discharging team, or provider) will be collected.

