### Power Analysis

Based on a power analysis, a sample size of 472 (236 Thrive participants and 236 usual care) for the outcome of readmissions, or a sample of 534 (267 Thrive participants and 267 usual care) for the outcome of ED visits, will yield 80% power to detect significance at the *P*<.05 level. Our goal is a sample size of 534 to ensure adequate power for both outcomes. This assumes a 20% (106/534) loss to follow-up rate. Furthermore, assuming at least a third of the patients will have SMI and an overall 30-day readmission rate of 28% (44/160), a sample of 534 patients will have 80% power to detect an odds ratio as small as 1.46, comparing those with and without SMI, to be statistically significant at the *P*<.05 level. Power analyses were conducted using Power Analysis and Sample Size 2021 (NCSS Statistical Software) [28].

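### The index hospitalization, and possibly day zero, is defined differently for Thrive and usual care, which can create a spurious readmission or ED difference in either direction

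*Protocol article*

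**What the plan says.** The outcomes include "30-, 60-, and 90-day readmissions and ED visits" (Variables and Measures), and the Aim-2 Analysis section makes readmission and ED use the subject of the primary model. Variables and Measures then gives each arm its own starting rule:

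- **Thrive:** "these outcomes will be assessed from the date of hospitalization that resulted in a referral to Thrive".
- **Usual care:** "all readmission and ED visits occurring after the first index hospitalization identified in the EHR from the calendar year of the study".

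Primary and specialty care visits have a single anchor for everyone, "receipt of primary and specialty care within 30 days of index hospitalization", which does not say whether the count starts at admission or discharge. Exposure is defined by uptake: "The primary independent variable is participation in Thrive". The primary model is a mixed-effects negative binomial regression with medical-team and time effects. The Results section places data collection between April 2024 and December 2025.

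**The concern.** The two rules differ in up to three ways.

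1. **Which stay.** A usual-care patient is indexed on the first stay of a year. A Thrive patient is indexed on whichever stay produced a referral. A patient indexed on a later stay has by definition been admitted before within the period, and frequent admission predicts further admission.
2. **Which day.** Read literally, the Thrive clock starts on the date of a hospitalization, while usual-care events are those after one. A readmission cannot occur while the patient is still in the index stay, so an admission-date start shortens the Thrive window.
3. **Which year.** The usual-care rule refers to one calendar year, but the study covers two.

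The comparison at stake is the primary one. If the arms are measured by different rules, the expected difference under no effect need not be zero, and neither a positive nor a null result can be read at face value.

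**Working it through.** **Inputs from the article.** The overall 30-day readmission rate is given as 28% (44/160 = 27.5%; Power Analysis). The target is 267 per arm. Index stays last over 24 hours (Study Population). Table 1 periods are 3 + 2 + 2 + 17 = 24 months.

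**Assumed, because not given.** Mean length of stay (LOS), and the share of Thrive patients indexed on a later stay.

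**Calendar.** Neither 24 months nor April 2024 to December 2025 fits in one calendar year. The usual-care rule could mean 2024 only, 2025 only, or the first stay in each.

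**Index stay alone** (discharge clock in both arms). The check was a simulation with no treatment effect. Admission rates vary between patients (gamma frailty, shape 0.15, 0.3 or 0.6), LOS is 5 days, and the mean rate is tuned so that first stays have about a 28% 30-day readmission risk. Usual care is indexed on the first stay of the year. Thrive is indexed on the stay at which referral happens, with a fixed referral probability per stay.

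| Referral probability per stay | Thrive indexed on a later stay | Usual care | Thrive | Difference (points) |
|---|---|---|---|---|
| 1 | 0% | 27.6 to 28.5% | identical | 0 |
| 0.5 | about 37% | 27.8 to 28.4% | 31.7 to 33.0% | +3.5 to +4.6 |
| 0.2 | about 61% | 27.5 to 28.6% | 36.4 to 40.2% | +8.2 to +11.6 |

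A positive difference is false harm. The first row also serves as the check on the remedy: with the same index stay and the same clock, the null difference is zero.

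**Clock alone** (Thrive from admission, usual care from discharge, no true effect). With constant hazard, h = −ln(0.72)/30, and the observed Thrive risk is 1 − 0.72^((30 − LOS)/30).

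- LOS 3: 1 − 0.72^(27/30) = 0.256; ratio 0.256/0.28 = 0.914.
- LOS 5: 1 − 0.72^(25/30) = 0.2395; ratio 0.2395/0.28 = 0.855.
- Front-loaded hazard (Weibull shape 0.8), exponent ((30 − LOS)/30)^0.8: ratios 0.931 and 0.883.
- LOS 1 to 10 days under constant hazard: Thrive reads 27.2% down to 19.7%, a false benefit of 0.8 to 8.3 points.

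The planned model is for counts, so the corresponding time-at-risk ratio is (W − LOS)/W. At LOS 5 this is 25/30 = 0.83, 55/60 = 0.92 and 85/90 = 0.94 for the three windows. In a simple two-proportion test at 267 per arm, the chance of a significant false benefit is 9% at LOS 3 and 19% at LOS 5, against 2.5% in that direction.

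**Both together at LOS 5.** The difference runs from −3.6 points (24.7% vs 28.3%, all referrals at the first stay) to +7.2 points (35.8% vs 28.6%, about 61% on later stays). In one case it is near zero (27.9% vs 27.8%).

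**Yardstick.** The article states no Thrive-versus-usual-care effect, so its 236 per arm for readmissions cannot be reproduced. If 28% is taken as the usual-care rate, with a two-sided 5% test, 236 per arm gives 80% power against about 17.2%, a difference of 28.0 − 17.2 = 10.8 points.

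**The case against.** The strongest objection is to the clock. The article elsewhere treats these outcomes as following discharge: the Background calls them posthospital use, and Cost-Benefit Data calls them postdischarge use. The usual-care sentence says which events are collected without naming a day zero. The Thrive wording may simply be loose, in which case the clock effect is nil. That stands: the clock figures are conditional on the admission-date reading. Figure 2 and Multimedia Appendix 3, which are not shown, may settle the windows.

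The index-stay effect also vanishes if every referral happens at the first stay. In addition, a first stay in a calendar year may itself follow an admission in the previous year, so the contrast is one of degree. Both points limit the size; neither aligns the rules.

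A reader might infer more than the text supports:

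- **That the rules necessarily produce a false benefit.** They do not. The two effects oppose each other and can cancel.
- **That usual-care events are counted without limit, or that patients referred later keep adding post-Thrive events indefinitely.** The 30-, 60- and 90-day windows are given for the outcomes generally, so any carry-over is bounded.
- **That usual-care stays after a unit's start of referrals contaminate the control group.** Under the stated exposure, participation, they do not. Whether to analyse by unit condition instead is a separate question about the estimand.

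**Conclusion.** The index-stay asymmetry is explicit in Variables and Measures, and the calendar reference is ambiguous. Medical-team and time effects act on who treated the patient and when. They do not equalise which of a patient's stays is chosen or how many days are at risk. Following the text as written can therefore give a non-zero difference under no effect.

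Direction and size cannot be fixed from the article. Later-stay indexing works against Thrive, by about 3.5 to 11.6 points if 37% to 61% of Thrive patients are indexed on later stays. An admission-date clock, if that is what is meant, favours Thrive, with risk ratios of about 0.91 and 0.86 at assumed stays of 3 and 5 days. Several points in either direction is material beside the roughly 11-point yardstick, which itself assumes a 28% usual-care rate. Confidence is high that the rules differ, moderate on the clock, and low on the net sign. This should be settled before the analysis planned for early 2026.

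**What to change.** Replace the two sentences with one rule for both arms:

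- **Index:** the patient's first eligible discharge home within stated study dates for the relevant period. Those dates replace the calendar-year reference.
- **Time zero:** the discharge date.
- **Counting:** readmissions and ED visits on days 1–30, 1–60 and 1–90 after discharge.
- **Adjustment:** admissions in the 12 months before the index stay, from the EHR.

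The text should also say how a patient first referred at a later stay is handled. The cost is revised EHR query logic and the loss of some later-stay referrals as index stays. Their number is not in the article and should be counted early, because each one lost is one fewer toward the 267 Thrive participants. The change does not require reclassifying patients by unit condition.

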### Analysis

Monthly reports will be generated to monitor referral patterns to the Thrive clinical pathway. The primary analysis will use a mixed-effects negative binomial regression model, accounting for both medical team and time effects, to evaluate readmission and ED utilization patterns comparing those with and without SMI who receive Thrive to those with and without SMI who receive usual care [26,27]. Sensitivity analyses may include logistic regression, depending on data distribution.

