### Current Usual Care

Usual care includes a discharge to the patient’s home with standard discharge care planning that addresses the patient’s medical needs. This may or may not encompass referrals to home care and other outpatient services as appropriate.

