### Thrive Intervention Group

Patients are referred to Thrive by nurse case managers or social workers during the hospital discharge planning process. They are alerted to a potential Thrive referral by an electronic health record (EHR) flag developed by our team [22]. Thrive participants agree to home care services through Penn Medicine at Home. A home care nurse visits the patient within 72 hours of discharge. This visit includes medication reconciliation, review of discharge orders, setting person-centered goals, and referral to other home care services (eg, physical therapy) as deemed necessary. The nurse also determines the visit frequency based on the patient’s needs, ranging from 1-3 visits per week. All Thrive participants receive a social work referral, and their psychosocial and mental health needs are further assessed and connections to community resources are provided. Home care nurses provide patient updates to the discharging provider (eg, a medical doctor or advanced practice provider) following the first home visit. Extended supervision by the discharging provider is provided for up to 30 days or until Thrive participants have been seen by their primary care provider. A key feature of Thrive is the intensive, equity-focused, 30-day case management provided during weekly virtual interdisciplinary case conferences. These meetings focus on assessing and addressing the SDOH such as housing, food insecurity, and substance use services as needed. If a source of primary care is absent, we work to link Thrive participants to community providers. Additional Thrive services will be provided as determined by the work group (Aim 1).

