### Data Collection and Sources

Clinical data, outcome metrics, and postacute care service use will be derived from the EHR at baseline and throughout the Thrive referral period. The characteristics of Thrive participants will be captured in weekly case conferences and stored in a University of Pennsylvania REDCap (Research Electronic Data Capture; Vanderbilt University) system database. Data for the usual care group will be derived from the EHR. The study timeline is outlined in the SPIRIT diagram (Figure 2).

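### The primary readmission and ED model gives no stated role to patient covariates other than SMI or to prior use, although its participation-based contrast leaves case mix unbalanced by randomisation

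*Protocol article*

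**What the plan says.** The Aim 2 Analysis section states: "The primary analysis will use a mixed-effects negative binomial regression model, accounting for both medical team and time effects". The contrast is described as "comparing those with and without SMI who receive Thrive to those with and without SMI who receive usual care". SMI status, a patient-level diagnosis taken from ICD-10 codes (Study Population), is therefore already in the comparison. The only sensitivity analysis named is an optional logistic regression, with no covariates given.

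Variables and Measures defines the exposure: "The primary independent variable is participation in Thrive". It also lists "Additional covariate data at both the patient (eg, demographics, comorbidities, or mental health diagnoses) and unit levels" for collection, without saying how they will be used. Data Collection and Sources adds: "Clinical data, outcome metrics, and postacute care service use will be derived from the EHR at baseline and throughout the Thrive referral period". Nowhere is a patient's use before the index admission named as a covariate.

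On how patients enter each group:

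- Thrive Intervention Group: referral comes from a case manager or social worker, and "Thrive participants agree to home care services through Penn Medicine at Home". Agreement to home care is also an eligibility criterion for referral (Study Population).
- Current Usual Care, on standard discharge planning: "This may or may not encompass referrals to home care and other outpatient services as appropriate".
- Design and Randomization: "There are 2 units at HUP-Cedar; using a random number generator, the first unit will be chosen".

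**The concern.** In an individually randomised trial, leaving prognostic covariates out of the model mainly costs precision. Here the issue is bias. Patients are grouped by whether they took part in Thrive, not by the unit-period that was randomised. Reaching the Thrive group takes a clinician's referral and the patient's agreement to home care, and the article states no matching condition for usual care. Two randomised units could not balance patient characteristics in any case.

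If participants differ from usual-care patients in age, comorbidity or earlier hospital use, a model with only team, time, Thrive and SMI terms attributes that difference to Thrive. Earlier admissions and ED visits matter most, because they are the pre-index values of the outcomes being modelled. The index rules in Variables and Measures add to the problem. Thrive patients are indexed at the admission that led to referral, and usual-care patients at their first identified hospitalisation in the study's calendar year. A Thrive patient can have had earlier admissions in that year, whereas a usual-care patient by construction has none identified. Prior use can thus differ between the groups through the definitions alone.

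**Working it through.** The article gives no figure on covariate adjustment to reproduce. The 472 and 534 in Power Analysis come without an effect size, event rate or dispersion for Thrive versus usual care. The odds ratio of 1.46 concerns SMI versus no SMI and does not bear on this point.

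**1. What the text fixes.**

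| Element | Role in the primary model as stated |
|---|---|
| Thrive, SMI | contrast |
| Medical team, time | accounted for |
| Demographics, comorbidities | collected, no role given |
| Pre-index admissions and ED visits | not named as covariates |

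**2. Case-mix bias, closed form.** Suppose a binary risk factor multiplies the event rate by g and has prevalence p1 in Thrive and p0 in usual care. If it is left out, the rate ratio is multiplied by (1 + (g − 1)p1) / (1 + (g − 1)p0). All values below are assumptions.

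- g = 2, 30% in both groups: 1.3/1.3 = 1.00, no bias
- g = 2, 40% v 30%: 1.4/1.3 = 1.08
- g = 3, 40% v 30%: 1.8/1.6 = 1.125
- g = 3, 20% v 30%: 1.4/1.6 = 0.875

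**3. The same by simulation.** Negative binomial, 267 per group, 600 replicates, assumed usual-care mean 0.35 and dispersion 1, true rate ratio 1.0:

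| g, prevalence | Unadjusted RR (rejection) | Adjusted RR (rejection) |
|---|---|---|
| 2, 40% v 30% | 1.08 (6%) | 1.00 (5%) |
| 3, 40% v 30% | 1.13 (10%) | 1.00 (5%) |
| 3, 20% v 30% | 0.87 (12%) | 0.99 (5%) |

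The standard error of a 5% rejection rate is √(0.05 × 0.95/600) = 0.9 points, so the 6% cannot be told apart from nominal.

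A second simulation gave both prior and post-discharge visits a shared underlying risk. Assumed values were a prior mean of 2, a post-discharge mean of 0.5, overdispersion of 1.5 and a shared risk 20% lower in Thrive, with no true effect. The unadjusted rate ratio was 0.80 with 24–27% rejection. Adding log(1 + prior visits) gave 0.89 to 0.94 with 6–11% rejection at prior–post correlations of 0.30 to 0.56. An error-prone measure of risk removes only part of the bias.

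**4. Precision.** If covariates explain a share R² of the variance, 80% power becomes Φ((1.960 + 0.842)/√(1 − R²) − 1.960). This gives 82%, 84%, 88% and 92% at R² of 5%, 10%, 20% and 30%. It is a linear-model approximation. In simulated count models the gain depended on the covariate:

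- Balanced binary covariate, true rate ratio 0.65: power 61.2% to 61.7% (g = 2) and 61.8% to 64.0% (g = 3)
- Prior-visit count, true rate ratio 0.63: 76.3% to 80.2%, 78.0% to 84.0% and 76.3% to 84.3% at correlations 0.30, 0.45 and 0.56

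None of the simulations included clustering or time terms.

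**The case against.** The strongest reply is that the Analysis section is a summary in a condensed article. It excludes no covariates. Variables and Measures calls the patient items covariates and lists them alongside the discharging team, and medical team does appear in the model. The full list may stand in an analysis plan that is not shown. This holds against the reading that the model adjusts for team and time alone: a reader might infer that, but the text does not say it. It does not remove the point. The section names an adjustment set, and that set, taken as written, fits a participation-based contrast badly.

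Three further objections stand in part:

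- Baseline in Data Collection and Sources may mean the three-month baseline period in Table 1, so a patient-level look-back is not established and would have to be added.
- Both units contribute control and intervention time, so fixed differences between units do not pass directly into the Thrive effect. That does not help with differences between participants and non-participants.
- Every size above comes from assumed values, and with balanced covariates the bias is nil.

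It is also fair to say that the root problem is selection into participation, which covariates reduce but do not cure.

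**Conclusion.** The point holds as a weakness in the model as stated, at the level of a recommended change and with medium confidence. The article gives no analytic role to patient covariates other than SMI, and does not name prior use, in a comparison where randomisation does not balance patients.

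Three stronger readings are not supported. The article does not say that patient covariates are excluded. It is not true that no patient characteristic enters, since SMI does. And it is not shown that the Thrive estimate will be biased or that material power is lost: the documents give no imbalance, covariate strength, prior–post correlation or direction. The range of about 0.87 to 1.13 for a true rate ratio of 1.00 rests on an assumed 10-point imbalance and a covariate rate ratio of 2 to 3. The simulated power gain runs from about 0.5 to 8 points depending on the covariate assumed, so precision is a secondary reason and the gain may be small. The main benefit is less case-mix bias.

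**What to change.** In the Aim 2 Analysis section, name these patient-level fixed effects for the readmission and ED models, next to the SMI, team and time terms already there:

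- age and sex
- a comorbidity score
- pre-index inpatient admissions and pre-index ED visits, for example log(1 + count) over the prior 12 months

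Date all of them at or before the index admission and take them from the EHR in both groups. Data Collection and Sources has Thrive characteristics recorded in weekly case conferences, which have no usual-care counterpart and should not supply these values. Carry the same terms into the logistic sensitivity model, and report the primary model without them as a sensitivity analysis. Settle the list before the analysis planned for early 2026 (Results), so that it is not chosen with outcomes in view.

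The cost is wording, an EHR look-back and a few degrees of freedom, with no new patients or visits. Prior use is seen only within the health system; Strengths and Limitations already notes this limit for usual-care outcomes. Adjustment is therefore partial, and the participation-based exposure and the differing index rules need to be addressed in their own right.

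### 30-day readmission is powered for SMI versus no SMI as a yes/no outcome with an odds ratio, but the primary model is negative binomial, so the stated power does not describe the primary analysis

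*Protocol article*

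**What the plan says.** Aim-2 Methods, Analysis, fixes the primary model for readmission and ED use: "The primary analysis will use a mixed-effects negative binomial regression model, accounting for both medical team and time effects". The comparison is described as "comparing those with and without SMI who receive Thrive to those with and without SMI who receive usual care". The only mention of a model for a binary outcome follows: "Sensitivity analyses may include logistic regression, depending on data distribution".

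Aim-2 Methods, Power Analysis, contains two separate statements.

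- For Thrive versus usual care it gives "a sample size of 472 (236 Thrive participants and 236 usual care) for the outcome of readmissions", a larger total for ED visits, and then "Our goal is a sample size of 534 to ensure adequate power for both outcomes". No event rate, effect measure or test accompanies these totals.
- For SMI versus no SMI it works from "assuming at least a third of the patients will have SMI" and "an overall 30-day readmission rate of 28% (44/160", and claims "80% power to detect an odds ratio as small as 1.46, comparing those with and without SMI". This is the only power statement that names 30-day readmission.

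Variables and Measures lists readmissions at 30, 60 and 90 days without saying whether each is any-versus-none or a number of events. For usual care it speaks of identifying every readmission and ED visit after the index stay, which leans towards counts. Standard errors robust to misspecified variance are not mentioned.

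**The concern.** A proportion of patients with an odds ratio describes a yes/no outcome. A negative binomial model describes a number of events, estimates a rate ratio, and assumes a variance at least as large as the mean. The two sections therefore describe different analyses of 30-day readmission, and the outcome definition does not say which is meant.

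Both readings have a cost. If the outcome is yes/no, its variance is below its mean, the model cannot represent that, and model-based inference is conservative: power is lost. If it is a count, the published odds-ratio power belongs to a different outcome on a different scale. Either way, a reader cannot tell from the article what the primary analysis of 30-day readmission can detect between patients with and without SMI.

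**Working it through.** **Inputs.** From Power Analysis: N = 534, SMI share one third (178 with SMI, 356 without), overall 30-day rate 28%, odds ratio 1.46, significance level 0.05, power 80%, loss to follow-up 20% (106/534, leaving 428). Assumed: two-sided test, independent patients, no team or time terms.

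**1. The plan's own figure.** Solve for two rates with odds ratio 1.46 that average 28%: (2/3)p0 + (1/3)p1 = 0.28 gives p0 = 0.254 (no SMI) and p1 = 0.332 (SMI).

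- SE of the log odds ratio = √[1/(356 × 0.254 × 0.746) + 1/(178 × 0.332 × 0.668)] = 0.200.
- ln 1.46 = 0.378, so z = 0.378/0.200 = 1.89.
- Two-sided power = Φ(1.89 − 1.96) ≈ 47%.

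The stated 80% does not reproduce. The variants tried were:

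| Variant, odds ratio 1.46 | Power |
|---|---|
| Two-sided, 28% overall | 47% |
| Two-sided, 28% in the no-SMI group | 49% |
| One-sided | 60–61% |
| Two-sided after 20% loss (N = 428) | about 40% |

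At N = 534 the smallest odds ratio detectable with 80% two-sided power is about 1.72 to 1.75. Detecting 1.46 needs about 1,188 analysed patients. Read as a risk ratio, 1.46 gives 77% power with 28% overall, so a mislabelled risk ratio is possible, but the article does not allow this to be confirmed.

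**2. Negative binomial model on a yes/no outcome.** At 28%, the variance is 0.28 × 0.72 = 0.2016, below the mean of 0.28. On 0/1 data the likelihood is highest at zero dispersion, so the model reduces to Poisson. For the log rate ratio:

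- Poisson model-based variance: 1/(n0p0) + 1/(n1p1).
- Correct binomial variance: (1−p0)/(n0p0) + (1−p1)/(n1p1).

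At a common rate of 28% the SE ratio is 1/√0.72 = 1.18. The actual two-sided type I error is 2[1 − Φ(1.96 × 1.18)] ≈ 0.02. In simulations of 40,000 trials per scenario (SMI contrast, 178 versus 356):

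| Scenario | Model-based NB (Poisson limit) | Robust Poisson | Logistic | Model-based SE ÷ correct SE |
|---|---|---|---|---|
| No difference, 28% (type I error) | 1.9% | 4.7% | 4.7% | 1.18 |
| Odds ratio 1.46 (power) | 34% | 49% | 48% | 1.20 |
| Odds ratio about 1.75; 24.1% vs 35.8% (power) | 69% | 81% | 80% | 1.20 |

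The lower end of the quoted SE range, 1.13, comes from an illustrative two-arm scenario with 236 per arm and rates of 28% versus 17.2%. The second rate there was chosen to give 80% power and is not in the article.

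**3. The same model on counts.** Two assumed patterns, both with 72% of patients having no readmission:

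- 24% one, 4% two: mean 0.32, variance 0.40 − 0.32² = 0.298, ratio 0.93 (slightly underdispersed).
- 20% one, 6% two, 2% three: mean 0.38, variance 0.62 − 0.38² = 0.476, ratio 1.25 (overdispersed, the case the model is built for).

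So if the outcome is a count, the direction of any error in the standard errors cannot be known in advance.

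**The case against.** The strongest reply is that the outcome is meant as a count, since Variables and Measures speaks of every readmission and ED visit, and that a negative binomial model is then a sound choice. That stands: the fault is the mismatch and the undefined coding, not the model as such. Even for yes/no data, robust standard errors would bring type I error back to about 4.7%, and they could be specified in an analysis plan not shown. That also stands, so the loss of power is conditional. The error is conservative in any case and creates no false positives. What the reply leaves untouched is that an odds-ratio power statement does not describe a rate-ratio primary analysis.

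Three stronger readings are tempting, and the documents do not support them.

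- A reader might infer that Thrive versus usual care is underpowered for the same reason. The odds ratio is stated only for SMI versus no SMI. The totals of 472 and 534 carry no rate or effect measure, so any loss computed for them (roughly 80% to 71% in the 28% versus 17.2% scenario) rests on an assumed effect.
- A reader might infer that the model will fail to return standard errors on yes/no data. In trial fits this depended on the fitting routine: one optimiser returned none in 60 of 60 data sets, while another returned them in 60 of 60 (convergence of each fit not checked). It is not a property of the plan.
- A reader might infer that the primary estimand will be chosen after seeing the data. The primary model is fixed; only whether the sensitivity analysis is run depends on the data.

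**Conclusion.** The point holds for the SMI comparison of 30-day readmission. Its stated power is on the odds-ratio scale for a yes/no outcome, the primary model is on the rate-ratio scale, and the model that would match is optional.

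If the outcome is yes/no and errors are model-based, they are about 1.13 to 1.20 times too wide, type I error is about 2%, and about 11 percentage points of power are lost (69% against 80% at an odds ratio of about 1.75). If the outcome is a count, the model is reasonable and only the power statement is misplaced. These sizes assume independent patients and omit team and time effects.

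Aligning the model with the power statement would not be enough, because 80% power at odds ratio 1.46 did not reproduce under any variant of the odds-ratio calculation tried. This should be corrected before analysis, but it threatens power and interpretability rather than the validity of a positive result.

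**What to change.** In Analysis, define 30-day readmission as any versus none and make mixed-effects logistic regression, or modified Poisson regression with robust errors, its primary model. Keep the negative binomial model with robust errors for readmission and ED-visit counts. If a count is intended for 30-day readmission instead, say so and keep the negative binomial model with robust errors. In either case, report the alternative model always, rather than conditionally on the data.

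In Power Analysis, restate the SMI power on the primary model's effect scale, giving the effect measure, sidedness and whether N is before or after loss to follow-up. If 1.46 was meant as a risk ratio, label it so.

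The cost is a wording change and one recalculation before the analysis planned for early 2026. Two small downsides follow: under the any-versus-none definition, a second readmission within 30 days counts only in the count analysis, and the restated power will look less favourable.
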